#### Secondary endpoint analysis

Secondary endpoints will be assessed by the respective two-group tests with a corresponding 95 % confidence interval. For each secondary endpoint specific statistical tests will be conducted. That is, for continuous outcomes the *t*-test will be used, for binary outcomes the chi-square-test and for time-to event outcomes the log-rank test. Secondary endpoint analyses are considered as exploratory. Subgroup analyses will be undertaken by checking interaction of covariates with intervention [38]. The trial will reported according to the guidelines of the consolidated standards of reporting trials (CONSORT) for randomized controlled trials. Adverse events will be reported as rates with corresponding 95 % confidence intervals. All adverse events (AEs) and serious adverse events (SAEs) will be given in lists.

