## Methods/Design

### Study design

SCAN is a prospective randomized controlled multi-center trial in adult patients with colorectal cancer (International Classification of Diseases, ICD-10 C18-20) in Union internationale contre le cancer (UICC) stage I-III. The study is conducted in the surgical wards of eight large and middle-sized cancer centers and general hospitals in Saxony-Anhalt and Saxony, Germany.

Patients randomly assigned to the intervention arm receive additional support by specially trained oncology nurses for eight weeks after discharge from hospital following surgical therapy. Allocation to either intervention or control group is performed with equal ratio. The following amendments were submitted to the local ethics committee and approved on June 4^th^ 2013:Expansion of eligibility criteria to UICC stage I andChange of the primary outcome from adjuvant chemotherapy utilization to HRQoL.

Both amendments are causally linked to one another. Prior to the amendment only patients with UICC stage II & III were eligible for trial inclusion because of the actual medical guideline for the treatment of colorectal cancer. According to this guideline, adjuvant chemotherapy is indicated in patients with UICC stage II and more advanced tumor states only. Due to upcoming effects of the establishment of the preventive colonoscopy as a standard benefit of the German statutory health insurance a noticeable shift regarding tumor stages is obvious. Studies, which were published after approval of the study by the sponsor show that colorectal cancer, despite of the low participation rate of the healthy general population is detected significantly more often in early stages (UICC I) [36, 37] than previous reference data suggested. Nevertheless, this positive effect leads to a significant reduction of the patients eligible for the study. With the additional inclusion of patients in the UICC stage I a rise of the case number of approx. 40 % could be achieved. At the same time, patients in UICC I are not indicated to adjuvant chemotherapy. As a result, widening the eligibility criteria had to be accompanied by changing the primary outcome. Since HRQoL had been defined as a central secondary outcome, the primary outcome was replaced by a former secondary one without changing elements or procedures of the intervention itself.

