### Secondary endpoints

An overview on primary and secondary endpoints and the study timeline is provided in Table 1:

**Table 1 Tab1:** Outcome measures and measure times

Measure times		T0	T1	T2
Outcomes & Instruments		Baseline (day before discharge)	Primary measurement (8 weeks after discharge)	Follow-up (8 months after discharge)
HRQoL (primary outcome)	EORTC QLQ-C30 + EORTC-QLQ CR29	x	x	x
Utilization of adjuvant chemotherapy			x (if appropriate)	x
Supportive Care Needs and individual resources	FU-T 37		x	x
Distress	Distress Thermometer (DT)		x	x
Symptoms and functional impairments	MD Anderson Symptom Inventory		x	x

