### Randomization

Randomization on an individual level, patient enrollment and group allocation will be performed by fax from the Institute of Medical Epidemiology, Biostatistics, and Informatics (IMEBI), Halle as an external and independent unit. Randomization will be stratified by center using blocks of variable length from a reproducible SAS PROC PLAN code. A consecutive analysis of non-responders and of the causes for changes in therapy regimes is intended additionally due to the high therapy-related impairments in wellbeing and quality of life during adjuvant chemotherapy.

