### Statistics

#### Primary endpoint analysis

The analysis of the primary outcome will obey to the intention-to-treat principle using generalized linear regression modelling and reported as relative risk with its according 95 % confidence interval. The model will be adjusted for cancer site, tumor stage, cancer therapy, ECOG performance status, age, sex and eventual previous neoadjuvant radiation therapies.

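### Exploratory secondary outcomes are compared by unadjusted two-group tests; using centre, and T0 for the QLQ scales if T0 precedes allocation, would give narrower intervals

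*Protocol article*

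**What the plan says.** The section Secondary endpoint analysis sets the general rule, "Secondary endpoints will be assessed by the respective two-group tests", each with a 95% confidence interval. It then names the tests: "for continuous outcomes the *t*-test will be used, for binary outcomes the chi-square-test and for time-to event outcomes the log-rank test". No covariate, baseline value or stratification factor is mentioned. It adds that "Secondary endpoint analyses are considered as exploratory".

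Table 1 (Secondary endpoints) marks the row "EORTC QLQ-C30 + EORTC-QLQ CR29" at T0, T1 and T2. FU-T, the Distress Thermometer and the MD Anderson inventory are marked at T1 and T2 only. The T0 column is labelled "Baseline (day before discharge".

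Under Randomization: "Randomization will be stratified by center using blocks of variable length". Under Study design: "The study is conducted in the surgical wards of eight large and middle-sized cancer centers and general hospitals".

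The only adjusted model is the one for the primary outcome: "The model will be adjusted for cancer site, tumor stage, cancer therapy, ECOG performance status, age, sex", plus any previous neoadjuvant radiation. It includes neither centre nor baseline quality of life.

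**The concern.** The primary endpoint reduces quality of life to a yes/no response at 10 points. The continuous QLQ-C30 and CR29 scores, and all results at 8 months, therefore carry the rest of the quantitative evidence on the trial's central outcome. For these scores the plan collects a T0 value, and the stated test does not make the best use of it.

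A t-test on follow-up scores ignores T0. A t-test on change uses T0, but with its coefficient fixed at 1, which is less precise than estimating the coefficient whenever the correlation is below 1. Neither version uses the centre strata in which patients were randomised. In an exploratory analysis the interval is the main product, so its width matters.

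**Working it through.** **The plan's own figure.** The article gives no precision for the secondary scales, so the reference is its sample size: 48% v 63%, 80% power, 185 per arm. Two-sided 5% is assumed, in line with the 95% intervals.
- Mean proportion 0.555. n = [1.960·√(2·0.555·0.445) + 0.842·√(0.48·0.52 + 0.63·0.37)]² / 0.15² = 171.1, which rounds up to 172 per arm.
- With continuity correction: (171.1/4)·[1 + √(1 + 4/(171.1·0.15))]² = 184.2, which rounds up to 185 per arm, 370 in total. The stated figure is reproduced.

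**Interval of the stated t-test on follow-up scores.** Half-width = 1.96·√(2/185) = 0.204 SD.

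**Effect of adjusting for T0.** Let r be the correlation between T0 and follow-up. It is not in the article; 0.3 to 0.6 is assumed, with equal variances at both times and a T0 unaffected by arm.
- Standard error against a follow-up t-test: √(1 − r²).
- Standard error against a change t-test: √((1 + r)/2).
- Patients per arm giving the t-test's precision once T0 is adjusted for: 185·(1 − r²).

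| r | ratio v follow-up t-test | ratio v change t-test | equivalent n per arm |
|---|---|---|---|
| 0.3 | 0.954 | 0.806 | 168 |
| 0.4 | 0.917 | 0.837 | 155 |
| 0.5 | 0.866 | 0.866 | 139 |
| 0.6 | 0.800 | 0.894 | 118 |

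Intervals are thus about 5% to 20% narrower than with a follow-up t-test, and about 11% to 19% narrower than with a change t-test.

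**Effect of centre.** With intraclass correlation ICC (assumed 0.02 to 0.10), the ratio is about √(1 − ICC): 0.990 at 0.02, 0.975 at 0.05 and 0.949 at 0.10, a gain of about 1% to 5%.

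**Simulation check.** 370 patients, eight equal centres, 1:1 allocation within centre, 3000 runs per scenario. Mean full width of the 95% interval, in SD:

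| r, ICC | follow-up t-test | + centre | + centre and T0 |
|---|---|---|---|
| 0.3, 0.02 | 0.408 | 0.405 | 0.386 |
| 0.5, 0.05 | 0.408 | 0.399 | 0.345 |
| 0.5, 0.10 | 0.407 | 0.388 | 0.336 |

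At r = 0.5 the type I error of the unadjusted t-test was 0.049, 0.044 and 0.037 for ICC 0, 0.05 and 0.10. It was between 0.047 and 0.051 with centre and T0 in the model. The t-test is therefore valid, and slightly conservative when centres differ.

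**Is T0 a true baseline?** Table 1 puts T0 on the day before discharge. The In-patient period section says that patients already in the intervention group have their first nurse visit on the second last day before discharge and another on the last day before it. The Intervention section makes the nurse available from the start of primary therapy. Read together, T0 could follow both allocation and first nurse contact. No section places T0 before randomisation.

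**The case against.** A t-test is a legitimate analysis of a randomised comparison, its interval already allows for chance imbalance, and these analyses are exploratory. All of this stands. A reader might infer that the planned tests are biased or give false positives; the documents and the simulation do not support that.

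The article does not say whether the t-test is on follow-up scores or on change. One therefore cannot say flatly that the baseline is ignored, only that neither version uses it efficiently.

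The timing of T0 is the strongest objection. If T0 is recorded after the first nurse visit, conditioning on it could remove part of the treatment effect, which a follow-up t-test would not do. This also stands, and it makes T0 adjustment conditional. It does not favour a change-score test, which has the same weakness. Centre adjustment is unaffected.

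Table 1 labels the QLQ row as the primary outcome and does not list its continuous scores as secondary endpoints. Treating them as secondary is an inference, though a reasonable one, since the primary endpoint is only the response on global health status at 8 weeks. The other questionnaires have no T0, so the baseline argument does not reach them.

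The gain in power can also be small. The planned 48% v 63% corresponds to 0.332 − (−0.050) = 0.38 SD of change on a normal scale. At r = 0.6 and 185 per arm, a normal approximation gives power of about 0.91 for the follow-up t-test, 0.96 for the change t-test and 0.98 with adjustment. The benefit lies mainly in interval width.

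Covariates may be left to an analysis plan that is not shown. Here, however, the article names the tests, so the choice can be reviewed.

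**Conclusion.** The point holds as a minor matter of precision. The stated tests are valid, but their intervals are wider than necessary. For the QLQ-C30 and CR29 scales the avoidable width is about 5% to 20% if the T0-T1 correlation is 0.3 to 0.6. Centre alone accounts for about 1% to 5% if the ICC is 0.02 to 0.10. Both ranges are assumptions. The gain at T2 depends on the T0-T2 correlation, which is also unknown. No gain was calculated for binary or time-to-event outcomes.

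The T0 part depends on T0 being completed before allocation and first nurse contact, which the article does not establish. The centre part needs no such condition.

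**What to change.** - Reconcile Table 1 with the In-patient period section, and state when T0 is completed relative to allocation and the first nurse visit.
- If T0 precedes both, analyse each continuous QLQ-C30 and CR29 score at T1 and T2 by a linear model on arm, T0 score and centre. Report the adjusted mean difference with its 95% confidence interval.
- If T0 may follow either, adjust for centre and pre-treatment covariates only.
- For FU-T, the Distress Thermometer and the MD Anderson inventory, include centre only.
- For binary and time-to-event secondary outcomes, use centre-stratified tests (Mantel-Haenszel, stratified log-rank).

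No new data are needed. The cost is the clarification of T0 timing, changed analysis wording, slightly more analysis work and the modelling assumption of a linear relation with T0.

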### Removal from the study

Subjects may refuse to participate in the study at any time without giving a reason. The following further reasons can lead to withdrawal of the study for single patients:Wish of the patient,non-compliance,Not the predictable health disturbances which force the patient to the withdrawal, according to the appraisal of the treating doctor,Death of the patient.

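### For scales measured at both 8 weeks and 8 months, the stated two-group t-test leaves the 8-week and baseline scores unused, which costs precision and gives no protection if symptom-related drop-out differs between arms

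*Protocol article*

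**What the plan says.** Under Secondary endpoint analysis, the protocol article states the rule "Secondary endpoints will be assessed by the respective two-group tests", each with a 95% confidence interval. It then assigns tests by outcome type: "for continuous outcomes the *t*-test will be used", and "for binary outcomes the chi-square-test and for time-to event outcomes the log-rank test". It adds "Secondary endpoint analyses are considered as exploratory". No repeated-measures model and no covariates are named for secondary endpoints.

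Table 1 schedules the FU-T, Distress Thermometer and MD Anderson Symptom Inventory at T1 and T2. The QLQ-C30 and CR29 are scheduled at T0, T1 and T2.

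The Primary endpoint analysis section says "The analysis of the primary outcome will obey to the intention-to-treat principle". The secondary section has no matching statement. Removal from the study says "Subjects may refuse to participate in the study at any time without giving a reason", and also lists non-compliance, health disturbances and death as grounds for withdrawal. The Sample size section allows for about 10% drop-out, without a split by arm or visit.

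**The concern.** These scales are repeated measures, but the named test handles one score per patient. A patient who answers at 8 weeks and is then lost contributes nothing to a plain T2 t-test, although the T1 score tells us something about the missing T2 score. The T0 score of the QLQ-C30/CR29 goes unused as well.

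Two things are at stake. The first is precision, which is lost whatever the reason for drop-out. The second is bias, if symptomatic patients leave more readily in one arm. The design makes that conceivable. The Intervention section gives the intervention arm weekly calls for eight weeks and nurse contact for up to eight months, while the withdrawal rules include health reasons. If symptomatic controls left more often, the remaining controls would look better than they should and a benefit at T2 would be understated. Stronger selection in the intervention arm would push the other way.

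**Working it through.** **The plan's own figure.** The article gives none for the secondary endpoints. Its primary sample size does reproduce. For 48% against 63%, two-sided 5%, 80% power, n = [1.96·√(2·0.555·0.445) + 0.842·√(0.48·0.52 + 0.63·0.37)]² / 0.15² ≈ 171. The continuity correction, (n/4)·[1 + √(1 + 4/(0.15n))]², gives 185 per arm as stated. So 203 recruited per arm is a fair starting point.

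**Assumptions (not in the documents).** Scores are in SD units, with higher meaning worse. 10% are missing at T1. The T1-T2 correlation is ρ = 0.6. The intervention effect is 0.2 SD at T1 and T2. Drop-out after T1 has probability p, with logit p = a + b·(T1 score) and b allowed to differ by arm. The intercept a = −1.9 gives about 22-24% missing at T2, and a = −2.9 gives about 15-16%.

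**Bias of the T2 t-test on observed scores.** With normal T1 scores, the mean T2 score of those retained in an arm shifts by −ρ·b·E[p(1−p)] / (1 − E[p]). The bias is the difference in this shift between arms.

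Worked case with a = −1.9 and slopes of 0.8 in controls and 0 in the intervention arm:
- Controls: E[p] = 0.155 and E[p(1−p)] = 0.121, so the shift is −0.6 × 0.8 × 0.121 / 0.845 = −0.069.
- Intervention: shift 0.
- Bias: 0.069 SD, against benefit.

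| Slopes (control, intervention) | Bias, about 22-24% missing | Bias, about 15-16% missing |
|---|---|---|
| 0.5, 0.5 | 0.003 | 0.002 |
| 0.8, 0.8 | 0.008 | 0.004 |
| 0.5, 0.2 | 0.026 | 0.011 |
| 0.8, 0.2 | 0.053 | 0.025 |
| 0.8, 0 | 0.069 | 0.031 |

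Simulation at 203 per arm agrees with these values. A joint model using T1, with T0 where available, had bias of at most about 0.004 SD in the same scenarios.

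**Scale of the bias.** With 203 × 0.77 ≈ 156 completers per arm, the standard error is √(2/156) = 0.113 SD. A bias of 0.07 SD is then about 0.6 of a standard error, and 0.02 SD about 0.2.

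**Precision when drop-out is unrelated to symptoms.** Let q be the share of T1 responders who also answer at T2. Using T1 alone multiplies the variance by 1 − ρ²(1 − q).
- 23% missing: q = 0.77/0.90 = 0.856, giving 0.948, or an SD ratio of 0.974.
- 15% missing: q = 0.85/0.90 = 0.944, giving 0.980, or an SD ratio of 0.990.

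Adjusting for T0, with an assumed T0-T2 correlation of 0.3, multiplies the SD by about √(1 − 0.09) = 0.954. At 23% missing the product is 0.974 × 0.954 = 0.929, so the t-test's sampling SD is 1/0.929 ≈ 1.08 times as large. At 15% missing it is 1/0.944 ≈ 1.06. Most of this gain comes from T0. For the FU-T, Distress Thermometer and MD Anderson Symptom Inventory, which have no T0 score, the gain is only about 1-3%.

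**If drop-out depends on the unseen T2 score.** Under harsher assumptions (10-30% loss in controls against 5-10% in the intervention arm, log-odds of drop-out rising by 1 per SD in controls), the completers' bias is 0.08-0.25 SD where rate or mechanism differs by arm. Using T1 lowers it only to 0.05-0.19 SD.

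**The case against.** The strongest reply is that the article assigns tests by outcome type and goes no further. A reader might infer that it prescribes a separate test at each visit on whoever returns the T2 form. The text does not say so. It defines no T2 analysis set and is silent on imputation, and imputing from T1 before a t-test would be compatible with it. Such detail is commonly left to the full protocol or analysis plan. Nor does stating intention-to-treat only for the primary outcome show a completers-only secondary analysis, because analysis by allocation and handling of missing values are separate matters. This part of the reply stands. What remains is narrower: the method that is named does not by itself use T1 or T0.

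A reader might also infer that the T2 differences will be biased, or that the t-test fails whenever drop-out is related to symptoms. Neither follows. Equal dependence in both arms gives about 0.01 SD or less. Nothing in the article shows unequal drop-out, and the Follow-up section asks all patients for the same questionnaires at the same times. The only drop-out figure is about 10% overall, lower than the rates assumed here, and lower loss means less bias.

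The point does not extend to every 8-month comparison. Disease-free survival, as a time-to-event outcome, goes to the log-rank test, which censors lost patients and does not discard them.

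The replacement has limits too. Patients with no post-baseline score still contribute nothing useful, and the model implicitly extends scores beyond death, which is a listed withdrawal reason.

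The analysis of non-responders mentioned under Randomization does not settle the matter in either direction: the term is not defined, no method is given, and nothing ties it to the T2 estimates.

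**Conclusion.** The point holds for the continuous questionnaire scales measured at both T1 and T2. The article names a method that leaves collected information unused where a standard alternative would use it. The possible bias at T2 is about 0.02-0.07 SD if symptom-related drop-out is clearly unequal between arms, and it is negligible if the dependence is equal. This rests on assumed values for drop-out, correlation and slopes. Milder inequality combined with 15% missing gives only about 0.01 SD.

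The precision loss does not need unequal drop-out. It is about 7-8% in sampling SD at the higher loss where a T0 score exists, and about 1-3% where none does. The consequence is small: the analyses are declared exploratory and the primary endpoint at 8 weeks is unaffected. This is an improvement worth making, not an error in the plan.

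**What to change.** For the QLQ-C30/CR29, FU-T, Distress Thermometer and MD Anderson Symptom Inventory scores, replace the t-test with one likelihood-based repeated-measures model per scale. Include arm, visit and arm-by-visit, with unstructured within-patient covariance. Add the T0 score where the same scale was collected, that is, for the QLQ-C30/CR29. Report the T1 and T2 contrasts with 95% confidence intervals. Leave the log-rank test for disease-free survival as it is.

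The cost is a change of wording and slightly more programming; no new data are needed. The model assumes that drop-out is explained by observed values (missing at random). If it depends on unseen T2 scores, bias is reduced but not removed, so a short sensitivity analysis of missing T2 scores is a sensible companion, together with a sentence on how deaths are treated.

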### Intervention

Feasible patients are assessed by the participating study centers and registered to the coordinating trial center. Patients meeting the inclusion criteria and signing a written informed consent are randomized into the study arms. Patients in the intervention group are offered an additional nursing intervention after discharge for 8 weeks. The intervention time-line was adjusted to the actual S3-guideline on the treatment of colorectal cancer regarding the recommended latest onset of adjuvant chemotherapy. The intervention consists of a standardized protocol-based telephone follow-up serving once per week to disclose patients’ current supportive needs and in order to detect therapy-related physical and psychological impairments as early as possible. Standardized protocols were developed beforehand to ensure both consistent assessment and patient information during the counseling. Additionally, the SCAN is at patients’ disposal for contact from the beginning of primary therapy during the inpatient stage to outpatient aftercare for up to eight months. The intervention covers the entire period of transition from acute clinical care to out-patient aftercare.

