### Out-patient period

During the outpatient intervention period the SCAN inquires therapy-related symptoms and functional limitations of patients regularly using patient-held records (PHR) in order to assist patients during the transition from inpatient acute care to outpatient aftercare. In the first eight weeks after hospital discharge obligatory telephone consultations are carried out by the SCAN. During the consultations the SCAN rates the urgency of unmet supportive needs, incorporates qualified help if necessary and supports communication of involved health care professionals. Support is provided in five categories of possible supportive needs following standardized protocols:Proper self-management strategies for physical and psychological symptomsPatients stating persistent physical or psychological symptoms are guided in effective self-assessment possibilities. Moreover, depending on the kind of symptom suitable self-management strategies are discussed by the SCAN.Warranty of care continuityThe entries in the PHR are discussed on the phone with a SCAN regarding critical incidents. Here, the individually determined critical events and processes are forwarded to attending hospitals or resident physicians in order to initiate treatments appropriate to the occurring problems and to call in or hospitalize patients. Additionally, patients have the possibility to call between telephone appointments in case of therapy-related complications and side-effects and of psycho-oncological or logistic problems. An early detection of therapy-related physical and psychological impairments also aims at optimizing treatment management by providing an almost real time feedback to the medical professionals.Informed decision makingBeginning at the in-patient consultations, detailed information on the therapy plan as well as alternatives is provided. Further information needs are addressed during the appointed telephone calls, depending on the occurrence of events in need for support, e.g. pharmacological and non-pharmacological supportive measures, or referred to qualified external health care professionals and self-help groups.ParticipationIn addition, within the entire out-patient intervention period, patients are guided in access to office-based oncology specialists and organizational or logistical barriers to medical treatment facilities are discussed with the SCAN. Furthermore, patients are actively encouraged to keep a high therapy adherence, especially in patients living in rural areas or the socioeconomically deprived.Psycho-social well-beingThe consultation is aimed individually on the patient. Counseling on psychological well-being pursues an improvement of the quality of life by the support of the psychic as well as the social functionality of the patient, which is possibly a prognostic factor for the overall survival [10, 27]. Thereby, special attention is paid to individual resources of the patients. Patients are aided in defining both useful individual and institutional resources, e.g. experiences of self-efficacy or available social security benefits.

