
### Follow-up

In order to determine differences in healthcare services utilization between intervention group and controls, all patients are asked to fill out additional written questionnaires at 8 weeks and 8 months after discharge from hospital. At both times, patient’s adherence to medical recommendations and completion of medical therapies is assessed as well.

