### Potential adverse events

The SCAN intervention with a non-invasive educational profile is considered to include no additional risk.

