### Auditing

To realize quality assurance the Institute for Health and Nursing Science as the coordinating center of the study will provide an advanced support for documentation and study management in the recruiting centers. Trained research staff will visit each center at least 4 times. Pre-study-visit (1): the practice team will be introduced into the trial procedures, qualification of practice staff and research capacities building and documentation will be checked. Study visit (2 & 3): support for follow-up and data management with special attention on reporting AEs and SAEs. Post-study-visit (4): final query management. Additional audits can occur at any time during or after completion of the study. Monitoring will be performed regularly by verifying key data (signed informed consent form, inclusion and exclusion criteria and key baseline data). The research staff will be trained in source data verification and will be supported in preparing standardized reports.

To ensure the implementation of the intervention, quality audits are being conducted in the intervention groups in all study centers based on the guidelines of the Royal Collage of Nursing [40] and the German Network of Quality Assurance in Nursing Care [41]. The audit is based on (1) regular monitoring of the trained nurses’ knowledge about the training module, and (2) on an additional comparison of nursing records with study documentation for 10 % of all included patients. Nurses who administer the interventions and assess the outcomes are aware of group allocation due to their participation in the training to manage the SCAN intervention. Patients are not informed about group assignment, but might be aware of it due to unmasking information from nurses. Group allocation perception of included patients will be assessed at follow-up.

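### Adverse-event rates are planned without limiting them to events found the same way in both arms, although only the intervention arm is asked about symptoms every week

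*Protocol article*

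**What the plan says.** The Secondary endpoint analysis section says: "Adverse events will be reported as rates with corresponding 95 % confidence intervals". It adds that all adverse events (AEs) and serious adverse events (SAEs) will be listed. It names no AE test and no source for the AE data.

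Contact after discharge differs by arm.

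- **Intervention arm.** The Intervention section describes a "standardized protocol-based telephone follow-up serving once per week" over eight weeks, with early detection of impairments as a stated purpose. Under In-patient period, these patients are trained to fill in a patient-held record (PHR), and critical events that should prompt contact are listed for each patient. Under Out-patient period, the nurse (the SCAN) asks regularly about symptoms and limitations from that record and passes critical events on to hospitals or physicians. In addition, "patients have the possibility to call between telephone appointments in case of therapy-related complications and side-effects".
- **All patients, and the only post-discharge study contact described for controls.** Under Follow-up, "all patients are asked to fill out additional written questionnaires at 8 weeks and 8 months after discharge from hospital".

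The one statement about AE reporting at the centres is under Auditing, where study visits 2 and 3 provide "support for follow-up and data management with special attention on reporting AEs and SAEs". It is not limited to one arm. Under Potential adverse events the article says: "The SCAN intervention with a non-invasive educational profile is considered to include no additional risk".

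**The concern.** How often and how actively patients are asked affects how many minor events are recorded. Here the intervention itself is active, repeated symptom inquiry, and controls have no counterpart to it. A plan to report rates from all recorded events, with no rule on source, allows an event noticed in a weekly call to count in one arm while the same event in a control goes unrecorded.

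In a randomised two-arm trial reported under CONSORT, such rates will be read arm against arm. Two misreadings are possible: an apparent excess of events for a programme expected to add no risk, or a true reduction in events hidden by better detection. The confidence intervals cover sampling error only and would not show either problem.

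**Working it through.** **1. Plan's own figures.** The article gives no AE rate, so there is none to reproduce. The only planned figure used below is the group size of 185 per arm (Sample size section). It can be reproduced from 48% v 63% with 80% power, assuming a two-sided 5% level, which the article does not state:

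- n = [1.960 × √(2 × 0.555 × 0.445) + 0.842 × √(0.48 × 0.52 + 0.63 × 0.37)]² / 0.15² = 171.1, rounded up to 172.
- With continuity correction: (171.1/4) × [1 + √(1 + 4/(171.1 × 0.15))]² = 184.2, rounded up to 185.

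**2. Study contacts after discharge, from the text.**

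| Period | Intervention | Control |
|---|---|---|
| First 8 weeks | about 8 calls + 1 questionnaire = 9 | 1 questionnaire |
| To 8 months | about 8 calls + 2 questionnaires = 10 | 2 questionnaires |

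Patient-initiated calls are not counted. Both arms also have a baseline quality-of-life measurement before discharge (Table 1).

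**3. What unequal capture would do.** All inputs in this step are assumptions. Let the true risk r be the same in both arms, with capture c_I in the intervention arm and c_C in controls.

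- Recorded rates are r × c_I and r × c_C, so the recorded risk ratio is c_I / c_C whatever the value of r.
- SE of the difference = √[p_I(1 − p_I)/185 + p_C(1 − p_C)/185].

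With c_I = 95% and r = 30%:

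| Control capture | Recorded rates | Risk ratio | Difference, points (95% CI) | Approximate chance of a significant difference at the 5% level |
|---|---|---|---|---|
| 90% | 28.5% v 27.0% | 1.06 | 1.5 (−7.6 to 10.6) | 5% |
| 70% | 28.5% v 21.0% | 1.36 | 7.5 (−1.3 to 16.3) | 39% |
| 50% | 28.5% v 15.0% | 1.90 | 13.5 (5.2 to 21.8) | 89% |

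The last column only gauges size, because the article plans no AE test.

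The absolute difference depends on the assumed risk. With 50% control capture it is 4.5 points (−0.8 to 9.8) at r = 10% and 22.5 points (13.0 to 32.0) at r = 50%.

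**4. The reverse problem.** A true risk ratio of c_C / c_I in favour of the intervention would be cancelled exactly: 0.90/0.95 = 0.95, 0.70/0.95 = 0.74 and 0.50/0.95 = 0.53.

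**The case against.** The strongest reply is that the article never says events from calls or the PHR enter the AE data. Its only statement on AE reporting concerns the centres and applies to both arms. PHR free text is assigned to a qualitative analysis. The AE source may well be set out in the full protocol, which a journal article condenses. This stands, and it makes the point conditional. It does not remove the point: the article does fix both a rate analysis with listings of all events and a surveillance scheme that differs by arm, and nothing in it keeps the two apart. Centre records are not clearly neutral either, since the nurse forwards critical events to the hospitals and physicians who may then call patients in.

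Four further replies also stand.

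- Table 1 lists outcome measures. The absence of an AE row there does not show that AEs go uncollected.
- No between-arm AE test or effect measure is named, so the planned reporting is descriptive.
- Symptom burden is measured with the same instruments in both arms at 8 weeks and 8 months (MD Anderson Symptom Inventory, QLQ-C30 and CR29). A symmetric comparison of symptoms therefore exists.
- The capture figures have no basis in the article. If capture is nearly equal, the distortion is negligible, as the 90% row shows.

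A reader might go further and infer that the rates are certainly not comparable and will make the intervention look less safe. The article does not support that. The AE source is not stated, deaths and admissions depend less on how often patients are telephoned, and a true benefit could offset or outweigh the detection effect.

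**Conclusion.** The point holds as a risk. As written, the plan allows AE rates by arm to rest on unequal ascertainment. If events learned through SCAN calls or the PHR are counted, rates of non-serious, patient-reported events may not be comparable. The ascertainment bias would probably run upward in the intervention arm; the direction of the observed difference is likely but not certain.

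The size is unknown. Spurious risk ratios of about 1.06 to 1.90 follow from assumed capture of 95% in the intervention arm against 90% to 50% in controls, with equal true risks. The unequal contact is clear from the text; the magnitude is illustration only. The primary endpoint is not affected. The change is worth making because the safety statement would otherwise be hard to interpret.

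**What to change.** In the Secondary endpoint analysis section:

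1. Base by-arm AE rates and their confidence intervals only on sources collected identically in both arms: an AE and readmission item added to the existing 8-week (T1) and 8-month (T2) questionnaires, plus SAEs documented by the hospitals.
2. List events known only from SCAN calls or the PHR separately, for the intervention arm, without a between-arm rate. The promised listing of all events is kept.
3. State that hospital admissions are not a fully neutral measure, because referral by the SCAN can itself change whether a patient is admitted.

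The cost is one item in two questionnaires already scheduled and a written rule on event source. The downside is that fewer minor events enter the comparative rates. The third step is a caveat for interpretation and does not remove the effect of referral on admissions.
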